#### Secondary outcomes

Differences between the 2 treatment groups in change from baseline of haemoglobin (Hb) level at 3, 6, 12, 24, 30 and 36 months and over the follow-up period.The differences between the two study treatment arms assessed in a time-to-first-event analysis of the following, all are measured every 3 months after randomised unless otherwise stated:
A composite of non-fatal myocardial infarction, non-fatal stroke, hospitalisation for heart failure or death from any causeAll-cause deathHospitalisation with any new diagnosis of infectionsHospitalisation with a principal diagnosis of infectionVascular access thrombosisPeripheral vascular disease and/or amputationsAll-cause hospitalisationFatal and non-fatal cardiovascular event (myocardial infarctions (MI), stroke and hospitalisation for heart failure (HF))Fatal or non-fatal MIFatal or non-fatal strokeHeart failure hospitalisationLength of hospital stayESA resistive Index (ERI), defined as average weekly erythropoietin (EPO) dose per kg body weight (wt) per average haemoglobin (Hgb), over a 3-month period (ERI = (EPO/wt)/Hgb))Serious adverse events
All serious adverse eventsAll hospital admissionsInfections associated with hospitalisationAll-cause mortalityIron overload (measured by magnetic resonance imaging (MRI) FerriScan^@^ of the liver) measured within 6 months post randomisation and at between 12 and 24 months post randomisationCost analysis: an analysis of the financial costs of the treatment will be performed assessing the costs of ESA, iron, hospital admissions and procedures for the duration of follow-up among all patients assigned to intravenous iron compared to no iron treatment.

#### Other outcomes assessed with non-randomized analyses

Assessment of *factors associated with high serum ferritin levels*: Association between ferritin and (a) other measures of iron status (serum hepcidin, transferrin saturation (TSAT), soluble transferrin receptor, percentage hypochromic red cells, reticulocyte haemoglobin content, liver iron), (b) Inflammatory markers (C-reactive protein (CRP), tumour necrosis factor alpha, interleukin 1 (IL1) and interleukin 6 (IL6)) and others (infection rates, CV events, hepatitis, medications, comorbidities, dialysis vintage, dialysis access, hospitalisations, time variation of ferritin)*Assessment of liver disease:* liver function tests *(*LFTs), hepatitis B status, ultrasound and FibroScan of the liver*Assessment of the comparability of the current ferritin assay platforms*: the Abbott ARCHITECT versus the Vitros® Ortho Clinical Diagnostics (OCD) platforms*Analysis of defined primary and secondary outcomes*: by average weekly dialysis attendance (according to both ordinal attendance group and using attendance as a continuous variable)*Analysis of defined primary and secondary outcomes*: by markers of inflammation

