A recent study showed that serum ferritin (200–500 μg/L) correctly reflected liver iron stores, as assessed by magnetic resonance imaging (MRI) (FerriScan®), in haemodialysis patients without overt inflammation or malnutrition [34]. The authors concluded that current ferritin target values should be lowered to avoid iron overload. However, ferritin levels in their patients were much lower than in our First Nations MHD patients [34]. Another study has the opposite conclusion that transferrin saturation and serum ferritin levels were poor markers of liver and cardiac iron deposition in MHD subjects [35]. In patients with high ferritin levels receiving iron treatment, it is crucial to monitor iron overload by measuring liver iron non-invasively with MRI-FerriScan® [36, 37]. Monitoring liver fibrosis (using FibroScan®) and cirrhosis is also crucial [31, 38–40]. Considering the high prevalence of diabetes mellitus and metabolic syndrome in the First Nations Australian population, it may be hypothesised that a high prevalence of hepatic steatosis and fibrosis exists as encountered in dialysis patients more and more frequently in developed countries as well as the dysmetabolic iron overload [6]. There is a need to identify those patients with these underlying liver diseases, to adapt iron dosage and to monitor the safety of IV iron in this setting. This peculiar safety issue seems particularly relevant since indiscriminate IV iron has recently been shown to either trigger or aggravate non-alcoholic fatty liver disease / non-alcoholic steatohepatitis in dialysis patients suggesting a double-edged iron sword [6].

In some studies, iron treatment has been associated with adverse effects (infections, cardiovascular complications and hospitalisations) especially if doses of > 1000 mg are given over 6 months [41]. Our patients are already at high risk of infections such as high rates of melioidosis during the wet season and high prevalence cardiovascular disease [42, 43].

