#### Secondary objectives

The secondary objectives are as follows: (1) to document serious adverse events – major cardiovascular events, rates of infections and all-cause hospitalisation rates associated with the intravenous iron therapy [2]. To assess the relationship between ferritin, total body iron levels, measures of iron status, inflammation and liver disease [3]. To determine the costs that associate with intravenous iron treatment in this setting.

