### Provision for post-trial care {30}

Participants found to have evidence of liver disease on ultrasound scans and/or FibroScans and those found to have iron overload on FerriScans will be referred to the liver clinics and haematologists respectively. All types of adverse events that occur from the day of randomisation to the end of follow-up will be reported to the sponsor and the participants’ usual clinical teams as soon as possible after the research staff identify the event. Participants will be given IV iron as per standard IV iron administration protocol post-trial as needed.

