#### Tertiary outcomes: comparison between the two treatment groups of the following all measured at every 3 months

Cumulative dose of ironSerum ferritin levelsTSATPlatelet countSerum albumin levels

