## Discussion

The INFERR clinical trial will address significant uncertainty on the safety and efficacy of iron therapy in First Nations Australians with ESKD with hyperferritinaemia and evidence of iron deficiency. This will hopefully lead to the development of evidence-based guidelines. It will also provide the opportunity to explore the causes of hyperferritinaemia. Anaemia, and particularly, iron deficiency anaemia, is common among First Nations ESKD patients from the NT. The coexistence of hyperferritinaemia, inflammation and chronic infections complicates the diagnosis and management of iron deficiency in First Nations patients with CKD/ESKD which the trial will address [6].

The study will also evaluate the significant issues on the performance differences in ferritin measurement platforms to determine clinical decision limits in people with CKD/ESKD [6]. Identifying and evaluating patients with hepatic diseases such as hepatic steatosis and non-alcoholic fatty liver disease (NAFLD) as seen in high prevalent diabetes mellitus, metabolic syndrome states, dialysis dependence and dysmetabolic iron overload will help to adapt iron dosage and to monitor the safety of IV iron therapy in this setting [54–56].

Indiscriminate IV iron therapy has recently been shown to either trigger or aggravate NAFLD in dialysis patients which warrants the evaluation in the INFERR clinical trial [38, 54].

The use of FerriScans, recently shown to accurately measure hepatic iron load in dialysis patients will provide useful information for decision, choice and follow-up of iron therapy in patients with hyperferritinaemia and evidence or iron deficiency [34, 36].

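### Fatty liver harm from IV iron is named for evaluation in the trial, but the liver disease measures sit under non-randomised analyses with no comparison by arm assigned

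*Protocol article*

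**What the plan says.** Under Background and Rationale {6a}, the protocol article writes: "This peculiar safety issue seems particularly relevant since indiscriminate IV iron has recently been shown to either trigger or aggravate non-alcoholic fatty liver disease". It gives the purpose of finding patients with liver disease as "to adapt iron dosage and to monitor the safety of IV iron in this setting". The Discussion repeats the concern about IV iron: "trigger or aggravate NAFLD in dialysis patients which warrants the evaluation in the INFERR clinical trial".

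The outcome lists treat liver disease differently:

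- Secondary objectives: the only objective that mentions liver disease is "To assess the relationship between ferritin, total body iron levels, measures of iron status, inflammation and liver disease".
- Secondary outcomes: liver iron by FerriScan appears. LFTs, ultrasound and FibroScan do not.
- Tertiary outcomes, framed as a comparison of the two groups: cumulative iron dose, ferritin, TSAT, platelet count and albumin.
- The liver disease item, which comprises LFTs and "hepatitis B status, ultrasound and FibroScan of the liver", stands under the heading "Other outcomes assessed with non-randomized analyses".

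The stated use of the scans is clinical. Under Provision for post-trial care {30}, "Participants found to have evidence of liver disease on ultrasound scans and/or FibroScans" are to be referred to liver clinics.

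**The concern.** Whether IV iron triggers or worsens fatty liver disease is a question about the effect of the randomised treatment. The plan assigns the measures closest to that question to analyses it calls non-randomised, and its one liver disease objective is an association. Liver findings related to ferritin or iron markers are open to confounding by metabolic syndrome, inflammation and hepatitis, all of which the article itself discusses. Identifying and referring patients helps those patients, but does not show whether allocated iron made their livers worse.

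At stake is the use of data that will be collected anyway. A comparison by allocated arm addresses the named harm more directly than the associations can. An analysis plan that followed the outcome lists as written would carry the mismatch forward.

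**Working it through.** **Where each liver measure stands**

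| Measure | Where it appears | Comparison by arm assigned? |
|---|---|---|
| Liver iron (FerriScan) | Secondary outcomes; about 100 willing participants (Table 1, note 3) | Yes, as a secondary outcome; measures iron load, not steatosis or fibrosis |
| LFTs | Other (non-randomised) outcomes; also among the monthly routine tests that may serve as outcomes or covariates | None assigned; the mixed model could take them |
| Hepatitis B status | Other outcomes; stratified analysis (i) | Only as a possible modifier of the treatment effect |
| Ultrasound, FibroScan | Other outcomes; Table 1 | None |

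The Statistical analysis plan section describes clinical, biochemical and outcome data by arm. That is a summary without an effect estimate. The mixed model stands under Analysing primary and secondary outcomes and names haemoglobin as its example, with no liver measure. The section on additional analyses models factors associated with ferritin and contains no analysis of liver disease by arm.

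**What a comparison by arm could show**

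The plan gives no figure of its own to reproduce here, and no SD or clinical threshold for any liver measure, so the results are in SD units. For 1:1 allocation, 80% power and two-sided 5%:

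- detectable difference = 2 × (1.960 + 0.842) / √N
- 95% CI half-width = 2 × 1.96 / √N

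*LFTs.* N = 576 × 0.95 = 547 (the plan's 5% drop-out).

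- Detectable difference 5.604 / √547 = 0.24 SD; half-width 3.92 / √547 = 0.17 SD.
- With the pre-randomisation value as covariate, multiply by √(1 − r²). Assumed correlations r = 0.3, 0.5 and 0.7 give 0.23, 0.21 and 0.17 SD.

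*Second scans.* Recruitment runs from 16 December 2020 to 30 June 2023, which is 926 days, and the project ends with 2023. Table 1, note 4, puts the second ultrasound/FibroScan at 12 to 18 months. To reach even 12 months, a participant must enter by 31 December 2022, which is day 745. With uniform accrual (assumed), 745 / 926 = 0.805, and 576 × 0.805 is about 463.

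- Ceiling, N = 463: 5.604 / √463 = 0.26 SD; half-width 0.18 SD.
- Uptake and survival to the scan are not given. Under assumed values, N = 463 × uptake × survival:

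| Uptake | Survival 85%: N, detectable SD | Survival 70%: N, detectable SD |
|---|---|---|
| 75% | 295, 0.33 | 243, 0.36 |
| 50% | 197, 0.40 | 162, 0.44 |
| 25% | 98, 0.57 | 81, 0.62 |

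The 12-month ceiling is favourable. Table 1 marks the second scan in the 24-month column. On that timing entry must fall by 31 December 2021 (day 380): 380 / 926 = 0.410, N is about 236, and the detectable difference is 5.604 / √236 = 0.36 SD before any loss to uptake or death.

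SD units suit FibroScan stiffness. They do not suit ultrasound steatosis if it is recorded as present/absent or as a grade.

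**Baseline.** LFTs are monthly routine tests, so a value before randomisation exists. The first scan may be taken up to 6 months after randomisation, hence after study iron in Arm A, and cannot serve as a baseline.

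**The case against.** The strongest reply is that this is an omission of the kind a condensed article leaves to the analysis plan. Several points support it:

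- The heading over the liver item is loose. Dialysis attendance is listed under it too and gets an interaction with treatment in the stratified analyses, and hepatitis B status enters stratified analysis (i).
- LFTs are named among routine tests that may be analysed as outcomes, and the mixed model with a fixed effect for arm fits a repeated continuous measure. The tertiary comparisons have no other model, so its reach may be wider than its subheading.
- Albumin, often part of an LFT panel, is already compared between groups, as is liver iron.
- The rationale and Discussion can be read as being about finding and managing patients with liver disease, and the cited harm concerns indiscriminate iron. Here iron is withheld above ferritin 2000 μg/L or at TSAT of 40% or more.
- The scans come from a consented, surviving subset with no pre-treatment value, so keeping them exploratory is defensible.

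Much of this stands. The heading does not strictly exclude a comparison by arm, and LFTs could be compared without breaching the text. It would be too strong to infer that the protocol forbids such comparisons or that liver safety goes unexamined.

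The mismatch remains because the article is not silent. It places the liver disease measures in a group labelled non-randomised, next to lists framed as differences between arms. Attendance has an explicit analysis with treatment elsewhere. The liver measures do not: hepatitis B is used only as a modifier, albumin is not presented as a liver disease measure, and FerriScan measures something else.

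**Conclusion.** The point holds as a cheap improvement, with medium confidence. A harm of the randomised treatment is named for evaluation, while the measures that bear on it are assigned to the weaker, associational kind of analysis. For LFTs the gap is one of assignment: they may be outcomes and a suitable model exists, but no section gives them a comparison by arm. For ultrasound and FibroScan there is none beyond possible description.

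A reader might infer that a planned result is biased or that the trial's conclusions are at risk. The document does not support that, since neither the primary outcome nor any listed between-arm comparison is affected.

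The benefit is modest. LFTs offer useful precision (about 0.24 SD, or 0.17 to 0.23 SD with baseline adjustment at the assumed correlations), but are only an indirect signal of steatosis or fibrosis. The scans are closest to the named harm but imprecise: 0.26 SD at the ceiling and 0.33 to 0.62 SD under the assumed uptake and survival, on uniform accrual and a scan at 12 months. Whether such differences matter clinically cannot be judged from the document.

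**What to change.** Add to the between-arm safety or tertiary outcomes:

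1. **Routine LFTs by allocated arm.** Use the planned linear mixed model on the post-randomisation values, with the pre-randomisation value as covariate, and report the estimate with a 95% CI. Label it a general, indirect liver signal, not a measure of steatosis or fibrosis. The covariate needs a stated exception, because the plan otherwise limits its models to arm (and time).
2. **Second-scan findings by allocated arm, as a supportive analysis only.** Compare FibroScan stiffness as a continuous measure and ultrasound steatosis as a proportion or grade. Do not use the first scan as baseline. Report, per arm, the numbers consented, alive, reaching the scan window and scanned, and note possible selection.

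Keep the association analyses and the referral pathway.

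The cost is a line or two in the outcomes section and a little more analysis. LFTs need no new data, and the scans are already scheduled for those who consent. The downside is one more safety comparison and a scan comparison that is imprecise and possibly selected, whose size depends on uptake and survival the document does not give.

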#### Tertiary outcomes: comparison between the two treatment groups of the following all measured at every 3 months

Cumulative dose of ironSerum ferritin levelsTSATPlatelet countSerum albumin levels

### Participant timeline {13}

The participant timelines and scheduled visits are shown in Fig. 2 and Tables 1 and 2.

**Table 1 Tab1:** Schedule of visits, data collection and follow-up

Visit day	Pre-screen	Day 1 baseline	3 M	6 M	9 M	12 M	15 M	18 M	21 M	24 M	27 M	30 M	33 M	36 M
Visit Window			± 2 weeks	± 2 weeks	± 2 weeks	± 2 weeks	± 2 weeks	± 2 weeks	± 2 weeks	± 2 weeks	± 2 weeks	± 2 weeks	± 2 weeks	± 2 weeks
Check eligibility	x	x												
Informed consent		x												
Demographic data		x												
Medical history		x												
Dialysis history		x												
Sociodemographic history		x												
Randomise		x												
Blood test results^1^	x	x	x	x	x	x	x	x	x	x	x	x	x	x
Additional iron studies pathology^2, 3^		x	x							x				
MRI scan (FerriScan)^3^				x						x				
Ultrasound/FibroScan of the liver ^4^				x						x				
Clinical outcomes data collection			x	x	x	x	x	x	x	x	x	x	x	x
Vital status (alive)		x	x	x	x	x	x	x	x	x	x	x	x	x
Procedures		x	x	x	x	x	x	x	x	x	x	x	x	x
Hospitalisations		x	x	x	x	x	x	x	x	x	x	x	x	x
Concomitant medication		x	x	x	x	x	x	x	x	x	x	x	x	x
Adverse events		x	x	x	x	x	x	x	x	x	x	x	x	x

^1^ Monthly routine blood test results will be reviewed at all scheduled study time points

^2^FBC, Retics, CYTOK, ADIPO, STFR and HPCD

^3^MRI (FerriScan) will occur within 6 months of randomisation and again between 12 and 18 months from day 1 on approx. 100 willing participants

^4^Ultrasound (FibroScan) will occur within 6 months of randomisation and again between 12 and 18 months from day 1

^5^A comparison of ferritin assays will be performed at 1 month post randomisation on a small number of participants

**Table 2 Tab2:** Study timelines

	2019				2020				2021				2022				2023			
Quarter	1	2	3	4	1	2	3	4	1	2	3	4	1	2	3	4	1	2	3	4
Finalisation of protocol																				
Development of eCRFs																				
Ethics applications																				
Protocol Amendment 1																				
Site preparation																				
Recruitment																				
Participants follow-up																				
Data cleaning and analysis																				
Writing of paper(s)																				

This project will run until the end of 2023, with a predicted recruitment period of 2.5 years (see Table 2).

### Sample size {14}

Maximal planned follow-up in the study will be 36 months (3 years). The 2-year rate of admission with first episode of infection or death in our patients on maintenance haemodialysis from 2000 to 2014 was 60%. In order to achieve a study power > 80% at 5% significance level in detecting a 30% reduction (from 60 to 48%) in the rate of first hospitalisation with all-cause infection or death, using the log-rank test (time-to-event modelling) assuming a 5% drop-out rate, 576 participants will be randomised 1:1 into each arm. The study also has > 90% power at 5% significance level of detecting a difference in haemoglobin of 5 g/L and standard deviation of 11.3 g/L based on published data [44, 45]. The sample size also provides enough power to determine differences within the ferritin strata.

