## Trial status

Protocol version number: INFERR trial protocol 2.0

Began recruitment: 16 December 2020.

Approximate date when recruitment will be completed: 30 June 2023.

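### The sample-size paragraph mislabels its effect as a 30% reduction and claims power within ferritin strata that the design does not have for the primary outcome; its overall power also assumes two years of follow-up for everyone

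*Protocol article*

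**What the plan says.** Sample size {14} takes its control rate from local data: "The 2-year rate of admission with first episode of infection or death in our patients on maintenance haemodialysis from 2000 to 2014 was 60" per cent. The target is "In order to achieve a study power > 80% at 5% significance level" for "detecting a 30% reduction (from 60 to 48%) in the rate of first hospitalisation with all-cause infection or death", by log-rank test, "assuming a 5% drop-out rate". The number given is 576, worded as if that many went into each arm; the abstract's Methods give 576 as the total. After a haemoglobin calculation (5 g/L, SD 11.3 g/L), the paragraph ends: "The sample size also provides enough power to determine differences within the ferritin strata". That sentence names no outcome, effect or stratum size.

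The strata are ferritin up to and above 1200 μg/L. They are used to stratify randomisation (Sequence generation {16a}) and again for a pre-defined secondary stratified analysis (Statistical methods {20a}).

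On timing, Participant timeline {13} says: "This project will run until the end of 2023, with a predicted recruitment period of 2.5 years". Trial status gives a recruitment start of 16 December 2020 and says: "Approximate date when recruitment will be completed: 30 June 2023". Maximum follow-up is 36 months.

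**The concern.** Three statements in one paragraph determine how the result will be read.

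- **Effect label.** The 30% and the two percentages printed beside it do not agree as a risk reduction. Taken literally, a 30% reduction from 60% is 42%, a much larger effect.
- **Strata sentence.** It is unqualified, and results by ferritin stratum will be reported. A reader told that the strata are adequately powered could take a null result in one stratum as evidence of no effect there.
- **Overall power.** The control rate is a two-year rate, but a participant recruited at the end of June 2023 can have at most about six months of follow-up before the project ends. If the event count falls short of the one assumed, a null overall result is less informative than the paragraph implies.

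**Working it through.** **Inputs.** Control risk 60% at 2 years, treated risk 48%, 5% drop-out, 576 in total, 5% significance (Sample size {14}). Two-sided testing is assumed, because sidedness is not stated and one-sided variants give totals of only about 425 to 500. Dates are from Trial status and Participant timeline {13}.

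**1. Effect size.** HR = ln(0.52)/ln(0.40) = 0.714, so the hazard reduction is 28.6%. Absolute reduction: 60 − 48 = 12 points. Relative risk reduction: 12/60 = 20%. An HR of exactly 0.70 gives 1 − 0.40^0.70 = 47.3%. A 30% relative risk reduction gives 42% (HR = ln(0.58)/ln(0.40) = 0.594).

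**2. The plan's own figure.** Events with two years for all: 576 × 0.95 × (0.60 + 0.48)/2 = 295. With |ln HR| = 0.3373, power = Φ(√(295/4) × 0.3373 − 1.96) = 82.6% (81.9% by Freedman's formula). A two-proportion calculation gives 270 per arm, or 540/0.95 ≈ 570. So 576 in total and more than 80% power reproduce on 60% versus 48%. Events needed for 80%: 4 × (1.960 + 0.842)²/0.3373² = 276.

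**3. Within a stratum, primary outcome.** Same effect, two years for all, events = 295 × stratum share:

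| Share of patients | Events | Power |
|---|---|---|
| 20% | 59 | 25% |
| 30% | 89 | 35.5% |
| 40% | 118 | 45% |
| 50% | 148 | 54% |
| 60% | 177 | 61% |
| two thirds | 197 | 66% |
| 80% | 236 | 74% |

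Reaching 80% needs 276/295, about 93% of all patients in one stratum, so no split gives 80% in both. A test of whether the effect differs between equal strata (HR 0.714 against 1.0) has about 30% power.

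The label matters here. Under the literal reading (60% to 42%), power would be about 99% overall and about 87% in a half-size stratum, so the strata sentence would look true at an equal split.

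**4. Within a stratum, haemoglobin.** Power = Φ(5/(11.3 × √(2/n)) − 1.96), n per arm. Half-size stratum, n = 144: Φ(3.75 − 1.96) = 96%. A 20% stratum, n = 57.6: Φ(2.37 − 1.96) = 66%.

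**5. Calendar.** Assumptions: exponential events with control hazard ln(2.5)/2 = 0.458 per year, uniform accrual from 16 December 2020 to 30 June 2023, 5% of patients removed (576 × 0.95 = 547.2). Event probability per arm = 1 − [exp(−λa) − exp(−λb)]/[λ(b − a)], where a and b are the shortest and longest follow-up.

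| Follow-up closes | a to b (years) | Event probability, control / iron | Events | Power, HR 0.714 | Power, HR 0.70 |
|---|---|---|---|---|---|
| 31 Dec 2023 | 0.50 to 3.04 | 0.530 / 0.423 | 261 | 77.8% | 81.9% |
| 30 Sep 2023 | 0.25 to 2.79 | 0.473 / 0.374 | 232 | 72.8% | 77.2% |
| 30 Jun 2023 | 0 to 2.54 | 0.409 / 0.320 | 199 | 66.3% | 70.9% |

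In the first row mean follow-up is 1.77 years (about 21 months), and about 41% of participants can reach 24 months.

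Sensitivity to accrual, closing on 31 December 2023 at HR 0.714: density falling linearly from 1.5 to 0.5 times the average gives 284 events and about 81%. The mirror image (slow start) gives 2 × 261 − 284 = 238 events and Φ(√(238/4) × 0.3373 − 1.96) = 74%.

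**The case against.** The best defence is that the calculation itself is right. Both percentages are printed, the method is a time-to-event test, and a 28.6% hazard reduction rounds to 30%. A reader might infer from the label that the sample size is wrong; step 2 shows that it is not.

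On the calendar, a reader might infer that 78% is the most the trial can reach. The documents do not support that. No accrual pattern is given, the bars of Table 2 are not visible, and the two earlier closing dates are assumptions. Front-loaded accrual or an HR of 0.70 restores just over 80% at the end of 2023, and counting events that occur before drop-out gives 269 events and 79.0%. The data safety and monitoring board is also asked to watch the sample-size assumptions ({21a}). All of this stands, and it limits the calendar point to a moderate, assumption-dependent one.

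On the strata, the sentence directly follows the haemoglobin calculation and could be meant for haemoglobin, and the ferritin comparison is already classed as secondary. But the sentence does not restrict itself to haemoglobin, and even for haemoglobin it fails at a 20% share.

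Two further inferences are unsupported. Nothing shows that the stratum above 1200 μg/L is the smaller one. Nor is power about 54% or less in every stratum: the larger of two unequal strata has more.

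**Conclusion.** The strata claim is not supported for the primary outcome: at the plan's own effect and full two-year follow-up, power is 25% to 74% for shares from 20% to 80%, and no split serves both strata. This rests only on the stated inputs and a two-sided 5% test. The 30% label is inaccurate as a risk reduction and only approximate as a hazard reduction, with no consequence for the total of 576.

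The overall power claim is correct if everyone has about two years of follow-up, which the stated dates do not provide. The shortfall is about 2 points in the central case, absent under favourable accrual or HR 0.70, and roughly 7 to 14 points at HR 0.714 if follow-up closes in September or June 2023. Those figures depend on the accrual and closing-date assumptions shown. The wording on arms is a slip: 576 in total is what reproduces, and Interim analyses {21b} treats 288 as half of recruitment.

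**What to change.** - **Effect.** State the target as a hazard ratio of about 0.71, that is 60% to 48% at two years (12 points; 20% relative risk reduction; 28.6% hazard reduction).
- **Strata.** Delete the sentence, or say that the trial is not powered for the primary outcome within ferritin strata, give power by expected stratum share, and call those results exploratory. If haemoglobin is mentioned, give about 96% for a half-size stratum and about 66% for one holding 20%.
- **Overall power.** Restate it from expected events on the actual accrual and follow-up closing dates. Tying the final analysis to about 276 primary events is an option.
- **Arms.** Write 576 in total, 288 per arm.

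The cost is protocol wording and less favourable stated figures, with no extra patients. The event-driven option costs more: under uniform accrual, 276 events would be reached in about late February 2024, past the stated project end.
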